## Abstract

**Background:**

Osteogenesis imperfecta (OI) is a rare bone fragility disorder associated with muscle weakness. Individuals with OI may therefore benefit from exercise interventions aiming to improve muscle and bone strength. Given the rarity of OI, many patients do not have access to exercise specialists who are familiar with the disorder. As such, telemedicine, the provision of health care through technology to provide care at a distance, may be well suited for this population.

**Objective:**

The main objectives are (1) to investigate the feasibility and cost-effectiveness of 2 telemedicine approaches for the delivery of an exercise intervention for youth with OI and (2) to assess the impact of the exercise intervention on muscle function and cardiopulmonary fitness in youth with OI.

**Methods:**

Patients with OI type I (the mildest form of OI; n=12, aged 12-16 years) from a pediatric orthopedic tertiary hospital will be randomized to receive a 12-week remote exercise intervention in either (1) a supervised group (n=6), monitored every session, or (2) a follow-up group (n=6), receiving monthly progress update appointments. Participants will undergo the following pre- and postintervention evaluations: sit-to-stand test, push-up test, sit-up test, single-legged balance test, and a heel-rise test. Both groups will be given the same 12-week exercise regimen, which includes cardiovascular, resistance, and flexibility training. For each exercise training session involving the supervised group, a kinesiologist will provide instructions to participants through live video sessions using a teleconferencing application. On the other hand, the follow-up group will discuss their progress with the kinesiologist every 4 weeks over a teleconferencing video call. Feasibility will be assessed by recruitment, adherence, and completion rates. A cost-effectiveness analysis of both approaches will be computed. Changes in muscle function and cardiopulmonary fitness will be examined between the 2 groups, pre- and postintervention.

**Results:**

It is anticipated that the supervised group will have higher adherence and completion rates compared to the follow-up group, which may be associated with greater physiological benefits; however, it may not be as cost-effective compared to the follow-up approach.

**Conclusions:**

By determining the most feasible telemedicine approach, this study may serve as a basis for providing increased access to specialized adjunct therapies for individuals with rare disorders.

**International Registered Report Identifier (IRRID):**

PRR1-10.2196/40262

## Introduction

Osteogenesis imperfecta (OI) is a rare congenital disorder characterized by bone fragility occurring in approximately 1 in every 10,000 individuals [1]. OI is typically caused by a dominant mutation in 1 of the 2 genes that code for the alpha chains in collagen type I*, COL1A1* and *COL1A2* [1]*.* The Sillence clinical classification of OI is divided into 4 phenotypic groups, with type I being the mildest and most frequently diagnosed [1,2]. OI type I comprises individuals with bone fragility and those whose stature falls within or close to normal limits [2,3]. While bone fragility is the leading characteristic of OI, we have shown that children and adolescents with OI type I have lower peak muscle force and muscle size compared to age- and sex-matched controls [4,5]. Given the positive relationship between muscle force and bone strength, muscle function deficits are likely to contribute to bone mass deficits in youth with OI [4-6].

For both healthy children and children with OI type I, exercise has been shown to be an effective method for improving cardiopulmonary fitness, as well as muscle strength [7,8]. Therefore, given the previously mentioned muscle deficits in children and adolescents with OI [4,5], individuals with OI type I may be more likely to benefit to a greater extent from this adjunct therapy, in addition to the typical mainstay of treatment, which includes rehabilitation programs, bisphosphonate therapy, and orthopedic surgery [9]. However, given the rarity of the disorder, many patients have challenges accessing exercise specialists who are familiar with the treatment of OI; thus, patients often seek or receive care from specialized tertiary hospitals. Attending both regular exercise training interventions in addition to frequent therapeutic visits at tertiary care centers may present a barrier for many patients, as specialized hospitals are often located in large urban areas, which can be far from patients’ homes.

Telemedicine is a method for the remote delivery of professional health services at a distance by linking clinicians and patients through information technology [10,11]. Lambert et al [12] used a telemedicine approach for the delivery of a 16-week home exercise program for pediatric acute lymphoblastic leukemia survivors. This supervised telemedicine approach was shown to be feasible, as the results demonstrated a mean adherence rate of 89% and a completion rate of 75% [12]. In contrast, Gagnon et al [13] used a follow-up telemedicine approach for the delivery of a 12-week home exercise program for youth with arthrogryposis multiplex congenita, where clinicians conducted follow-ups with study participants every 3 weeks. The results showed a 68% adherence rate and a 64% completion rate, which was sufficient for most study participants to achieve their goals [13]. As the recent literature demonstrates, the follow-up approach may be less effective as it led to a lower completion rate [12,13]. However, additional clinician time cost associated with the supervised approach may exceed the increase in benefits associated with constant supervision.

There remains a gap in the literature with respect to the comparison between supervised and follow-up telemedicine approaches and the associated cost-effectiveness of both approaches. Hence, the aim of this study is to evaluate the feasibility and cost-effectiveness of 2 telemedicine approaches (supervised vs follow-up) for the delivery of a home exercise program. The secondary aim of the study is to investigate the effectiveness of the home-based exercise program on muscle function and cardiopulmonary fitness in youth with OI type I. Given the aims of this study, it is hypothesized that participants in the supervised group will have higher adherence and completion rates compared to the follow-up group, which will be further associated with greater increases in muscle strength and cardiopulmonary fitness from the exercise intervention. However, the additional intervention delivery time required for the supervised group may make it less cost-effective compared to the follow-up approach.

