## Methods

### Study Design

This pilot study examines the feasibility of delivering an exercise intervention to a pediatric and youth population with OI by means of telemedicine. Study participants will be randomized into 1 of 2 telemedicine approach groups: (1) the supervised group and (2) the follow-up group. Given the COVID-19 pandemic, this protocol was designed to be conducted remotely, including the assessments. Therefore, simple clinical tests rather than hospital-based evaluations, which require cutting-edge technology, were favored.

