### Participant Eligibility

Individuals with a diagnosis of OI type I based on clinical evaluation and genetic mutation who are followed at a tertiary pediatric orthopedic hospital, ranging in age from 12 to 16 years, will be invited to participate in this study. Inclusion criteria encompass (1) confirmed genetic mutation in *COL1A1* or *COL1A2* genes; (2) medical approbation to initiate an exercise program by the patient’s treating physician; (3) the ability to communicate in either English or French; and (4) the availability of the internet, a webcam, and a microphone. The exclusion criteria include (1) fractures of long bones in the lower or upper limbs within the past 12 months, (2) fractures of the spine within the past 12 months, (3) lower and upper limb long bone or spinal surgery within the past 12 months, and (4) location outside of the province of Quebec due to professional license restrictions.

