### Evaluations and Intervention

#### Overview

The duration of the study is 16 weeks: 12 weeks for the intervention and 2 weeks at the beginning and end for evaluations. All participants will be given an exercise program to be completed at home. Both groups will use the teleconferencing application Microsoft Teams (version 1.3.00.28, Microsoft Corp). The supervised group will be monitored every session, while the follow-up group will receive feedback every 4 weeks.

Previous to the intervention, participants will be provided with initial testing and tutorials on the telemedicine application (Microsoft Teams) and the activity and heart rate monitor (Polar A370 watch; Polar Electro). Participants will be mailed the required equipment, such as the Polar A370 activity monitor (Polar watch), a 5-pound exercise ball, and a resistance band. All attempts possible have been made to ensure this study uses a minimal amount of equipment in order to reach a larger population that may have limited access to resources while also ensuring no sacrifices are made to the overall quality of the study. Both video and written instructions in English and French will be available to participants throughout the study. Instructions for the following will be included: telemedicine connections, completion of questionnaires, and Polar watch details (Bluetooth and USB connections, charging, and data transfer). Additionally, all study participants will have access to the 12-week exercise plan throughout the entire study. The exercise plan includes an illustration, video, and written description of each exercise, as well as 2 easier and 2 more difficult modifications for each movement (Figure 1). The exercise plan comprises 6 warm-up exercises, 7 to 8 exercises that will be repeated 3 times, and 5 cool-down stretches.

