### Statistical Analysis

As this is a feasibility study, the testing procedure will be assessed rather than only focusing on the potential outcomes of the intervention. To determine the optimal clinical practice of telemedicine for an exercise intervention, recruitment, adherence, and completion rates of 2 randomized groups (supervised and follow-up approaches) will be investigated. Descriptive statistics will be presented as means and SDs. Based on previous research on home-based exercise interventions [23], the adherence rate will be assessed with a set threshold of 80%. A Wilcoxon rank sum test will be used to evaluate the adherence rate and compare both telemedicine approaches. Whereas both recruitment and completion rates will be compared using descriptive statistics and assessed with a set threshold of 50%. To measure the change in outcome parameters of participants’ muscle strength and cardiopulmonary fitness, pre- and postintervention evaluation results will be assessed with a Friedman ANOVA. A Kruskal-Wallis test will be used to determine the differences in outcome parameter changes between the 2 groups (supervised and follow-up groups).

To assess the cost-effectiveness of the 2 telemedicine approaches, a cost-effectiveness plane and an incremental cost-effectiveness ratio will be computed. The incremental cost and incremental effect will be plotted on a cost-effectiveness plane, where the horizontal axis will represent the incremental cost and the vertical axis will represent the incremental effect [24,25]. The costs and clinical outcomes for both telemedicine groups will be plotted on the plane, which will visually demonstrate the additional cost per unit of health gain for each telemedicine approach. To calculate the incremental cost-effectiveness ratio, the difference in costs will be divided by the difference in mean performance outcomes between the supervised and follow-up groups.

Finally, as OI is classified as a rare disorder [1], analyses will be carried out with a significance level (α) of 0.10 [26]. Statistical analyses will be conducted using the statistical analysis software SPSS, version 25 (SPSS Inc).

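### The secondary aim claims effectiveness of the exercise programme, but both arms exercise and it is assessed only by uncontrolled pre-post change, so growth and test familiarity cannot be separated from exercise

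*Protocol article*

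**What the plan says.** The Introduction sets the secondary aim: to "investigate the effectiveness of the home-based exercise program on muscle function and cardiopulmonary fitness in youth with OI type I". The Abstract (Objective) places the same target among the main objectives: "to assess the impact of the exercise intervention on muscle function and cardiopulmonary fitness in youth with OI". The Discussion (Overview) repeats the aim and calls it the effect of the programme.

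On the arms, the Abstract (Methods) says: "Both groups will be given the same 12-week exercise regimen, which includes cardiovascular, resistance, and flexibility training". Study Design says: "Study participants will be randomized into 1 of 2 telemedicine approach groups: (1) the supervised group and (2) the follow-up group". No non-exercising, usual-care or wait-list arm is described, and no repeated baseline, external reference or growth adjustment.

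The Evaluations overview assesses the programme's impact by comparing pre- and postintervention evaluations. Under Statistical Analysis, "pre- and postintervention evaluation results will be assessed with a Friedman ANOVA", with alpha set at 0.10. A Kruskal-Wallis test compares the changes between the two delivery groups.

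Participants are young people "ranging in age from 12 to 16 years, will be invited to participate in this study". On timing: "The duration of the study is 16 weeks: 12 weeks for the intervention and 2 weeks at the beginning and end for evaluations". The two evaluations therefore lie roughly 12 to 16 weeks apart. The Sit-to-Stand Test section also defines a work index, repetitions multiplied by body weight in kilograms.

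**The concern.** Effectiveness of a programme means the outcome with it compared with the outcome without it. Here every participant has the programme, so the randomised contrast concerns how it is delivered, not whether exercise works. What remains for the effectiveness aim is a single-cohort comparison over time.

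Two rival explanations come with the population and the tests. Adolescents grow over the interval, and the work index rises with weight even if the repetitions do not change. The push-up, sit-up, balance, sit-to-stand and heel-rise tests depend on effort and technique, so having done them before can improve the second result.

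At stake is the interpretation. The Discussion expects the results to show how young people with OI respond physiologically to exercise. A significant pre-post change would naturally be read that way, although the design cannot tell training from growth or practice.

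**Working it through.** **Set the aim against the design**

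| Element | What the article fixes | What it can support |
|---|---|---|
| Secondary aim | Effectiveness, impact or effect of the programme | Needs an exercise versus no-exercise contrast |
| Arms | Supervised and follow-up, same regimen | A contrast of delivery mode |
| Between-arm test | Kruskal-Wallis on changes | Randomised inference about delivery mode |
| Pre-post test | Friedman ANOVA, two time points, alpha 0.10 | Whether scores changed, not why |

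No entry in the right-hand column isolates exercise. An analysis plan could not repair this, because no non-exercising participants are enrolled.

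**Work index**

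The index is repetitions × weight. With repetitions fixed, its relative change equals the relative change in weight. Assumed values, not in the documents: 30 repetitions at 45 kg give 30 × 45 = 1350. After a 1.5 kg gain, 30 × 46.5 = 1395, a rise of 1.5/45 = 3.3%. A 0.5 kg gain gives 1365, or 1.1%. Performance is the same in each case.

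**Illustration of the pre-post test**

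The article states no effect size, SD or power, so there is no planned figure to reproduce.

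Inputs from the article: n = 12 (6 + 6), two time points, alpha 0.10. Assumptions: no exercise effect, no ties, both arms pooled, a two-sided test, normally distributed individual changes, and a non-exercise drift of d SDs of the individual change.

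1. With two time points and no ties, Friedman's statistic is (n₊ − n₋)²/n, which is a sign test. The chi-square cut-off on 1 df at 0.90 is 2.706.
2. With 9 of 12 improving, the statistic is (9 − 3)²/12 = 3.00, which rejects. With 8 of 12 it is (8 − 4)²/12 = 1.33, which does not. The asymptotic test therefore rejects at 9 or more, or 3 or fewer.
3. At zero drift the rejection probability is 2 × (220 + 66 + 12 + 1)/4096 = 2 × 299/4096 = 14.6%. This exceeds the nominal 10% before any drift is added, because the chi-square approximation is poor at n = 12.
4. The exact sign test rejects at 10 or more, or 2 or fewer: 2 × (66 + 12 + 1)/4096 = 2 × 79/4096 = 3.9% at zero drift.
5. With drift d, the probability that a participant improves is p = Φ(d), and the number improving is binomial(12, p).

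| d (assumed) | p = Φ(d) | Asymptotic Friedman, n = 12 | Exact sign test, n = 12 | One arm, n = 6 |
|---|---|---|---|---|
| 0 | 0.500 | 14.6% | 3.9% | 3.1% |
| 0.1 | 0.540 | 16.1% | 4.6% | 3.4% |
| 0.3 | 0.618 | 27.6% | 10.6% | 5.9% |
| 0.5 | 0.691 | 46.8% | 23.3% | 11.0% |
| 0.8 | 0.788 | 76.2% | 51.7% | 24.0% |

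These are rejections in either direction. At d = 0.3, about 26.5 of the 27.6 percentage points are apparent improvement. In one arm of 6, both versions reject only if all six move the same way.

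Each column should be read against its own first row. At d = 0.5 the asymptotic test goes from 14.6% to 46.8%, and the exact test from 3.9% to 23.3%.

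**The case against.** The strongest reply is that this is a 12-person pilot. Feasibility and cost-effectiveness come first, the stated thresholds (80% adherence, 50% recruitment and completion) apply to feasibility rates, and no success criterion rests on the pre-post test. The outcome hypothesis is between arms, and the plan already includes a between-arm test of change. The limitations also call the data preliminary, and name the outcome-change data together with the small sample as reasons for caution. All of this stands and lowers the weight of the point. It does not remove it: an effectiveness aim is still stated and given a significance test, and the limitations mention neither the absent comparator nor growth nor test familiarity. A larger trial of the same design would have the same attribution problem.

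The size of the effect is also open to challenge. The documents contain no growth or retest data. At 0.1 SD drift the asymptotic rejection rate is 16.1%, barely above 14.6%. The article does not say whether the Friedman test is pooled or by arm, asymptotic or exact. This stands too: the table illustrates the problem and does not measure it.

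Two stronger inferences are tempting, and the documents do not support them:

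- **Regression to the mean.** Eligibility rests on diagnosis, age, medical approval, language, technology, fracture and surgery history, and location. Nobody is selected for low strength or fitness, so no shift in the group mean from this source is expected.
- **A significant pre-post result as the trigger for a larger study.** The limitations say that preliminary data will inform a larger study. They do not make this depend on significance.

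**Conclusion.** The point holds as a mismatch between the stated aim and the design. The planned pre-post analysis can show that scores changed during the programme, but cannot attribute the change to exercise. That conclusion needs only that growth and test familiarity are inseparable from training here. It does not depend on any drift value.

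The size is uncertain. Under assumed drift of 0.3 to 0.8 SD, with 12 participants pooled and no exercise effect, rejection runs from about 28% to 76% (asymptotic, against 14.6% at zero drift) or from about 11% to 52% (exact, against 3.9%).

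A reader might infer that the randomised comparison is compromised or that a control arm must be added. Neither follows. The supervised versus follow-up difference in change remains a randomised contrast, and a pilot may reasonably describe change without a non-exercising arm, provided it does not call the result effectiveness.

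**What to change.** 1. Restate the secondary aim in the Abstract, Introduction and Discussion as describing change in muscle function and cardiopulmonary fitness during the programme.
2. In Statistical Analysis, report pre-post results as paired change with a 90% interval, which matches alpha 0.10, and make no effectiveness claim from them.
3. Confine causal inference to the randomised supervised versus follow-up difference in change.
4. Bring the Discussion's statement about the physiological response to exercise into line with this.
5. Add to the limitations that there is no non-exercising comparator, that participants are growing (noting that the work index rises with body weight), and that repeated testing may itself improve scores.

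The cost is text in the aim, analysis, discussion and limitations. Design, sample size and data collection stay the same. The trial gives up a claim that its design cannot support.

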## Methods

### Study Design

This pilot study examines the feasibility of delivering an exercise intervention to a pediatric and youth population with OI by means of telemedicine. Study participants will be randomized into 1 of 2 telemedicine approach groups: (1) the supervised group and (2) the follow-up group. Given the COVID-19 pandemic, this protocol was designed to be conducted remotely, including the assessments. Therefore, simple clinical tests rather than hospital-based evaluations, which require cutting-edge technology, were favored.

### Participant Eligibility

Individuals with a diagnosis of OI type I based on clinical evaluation and genetic mutation who are followed at a tertiary pediatric orthopedic hospital, ranging in age from 12 to 16 years, will be invited to participate in this study. Inclusion criteria encompass (1) confirmed genetic mutation in *COL1A1* or *COL1A2* genes; (2) medical approbation to initiate an exercise program by the patient’s treating physician; (3) the ability to communicate in either English or French; and (4) the availability of the internet, a webcam, and a microphone. The exclusion criteria include (1) fractures of long bones in the lower or upper limbs within the past 12 months, (2) fractures of the spine within the past 12 months, (3) lower and upper limb long bone or spinal surgery within the past 12 months, and (4) location outside of the province of Quebec due to professional license restrictions.

### Ethical Considerations

Study approval was granted by McGill University’s Faculty of Medicine and Health Sciences Institutional Review Board (A01-M01-17A). Informed consent forms will be provided for participants aged 14 years and older. Any participant younger than 14 years will be asked to sign an assent form. Additionally, for those younger than 14 years, parents or caregivers will be required to sign a parental consent form as per Quebec’s provincial regulations. Individuals who meet the study inclusion criteria and agree to participate in the research study will be deidentified and assigned a study ID number. Direct subject identifiers will be stored as key codes and kept separate from the study data set. Patient’s medical record number, date of birth, and corresponding study ID number will be saved in a password-protected file that will be stored on a hospital computer in the office of the principal investigator. The key code will be the only link that reidentifies the study participant to their health information; all other patient data will be deidentified. All study records will be retained and stored in the principal investigator’s office for 7 years. Study participants will not receive compensation for their participation.

